##### GRV evolution and number of side effects of the enteral formula

GRV and adverse side effects caused by the enteral formula are listed among secondary outcome measures and will be assessed and documented by the nurse responsible for the study patient.

##### Glucose, urea and IGF-1 evolution over study period

Glucose, urea and IGF-1 will be measured together with daily routine blood analysis over the study period.

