**Day 2**													
Protein dose^1^	0.4			0.4			0.4			0.4			
Flow rate^2^	200–360			200–360			200–360			200–360			
Total protein^3^	1.4			1.6			1.6			1.6			

*GRV* gastric residual volume

^1^[g/kgBW/30 min], 4 nutrition cycles/24 h: each with 30 min nutrition followed by a 4-h break and 30 min GRV measure, night time break of 4 h. Total time of feeding, 2 h; GRV measurements, 2 h; break, 20 h

^2^[ml Fresubin© Intensive/30 min], depending on bodyweight

^3^Total of administered protein of the preceding 24 h [g/kgBW]

**Table 2 Tab2:** Continuous feeding protocol (control group)

Time	06:00–11:00	11:00–12:00	12:00–17:00	17:00–18:00	18:00–23:00	23:00–00:00	00:00–05:00	05:00–06:00
	Nutrition	Break + GRV	Nutrition	Break + GRV	Nutrition	Break + GRV	Nutrition	Break + GRV

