**Day 2**								
Protein dose^1^	0.4		0.4		0.4		0.4	
Flow rate^2^	40–72		40–72		40–72		40–72	
Total protein^3^	1.0		1.3		1.5		1.6	

*GRV* gastric residual volume

^1^[g/kgBW/5 h], 4 nutrition cycles/24 h: each with 5 h nutrition followed by a 30-min break and 30 min GRV measure, no night time break. Total time of feeding, 20 h; GRV measurements, 2 h; break 2 h

^2^[ml Fresubin© Intensive/h], depending on bodyweight

^3^Total of administered protein of the preceding 24 h [g/kgBW]

The experimental group will receive a calculated amount of enteral nutrition over 30 min, whereas the control group will receive the same amount over 5 h. After a 4.5-h break in feeding in the experimental group and a 1-h break in feeding in the control group, the next feeding cycle will begin. The experimental group will have a 4-h break at night.

The experimental group will start with 0.1 g protein/kg BW and will receive 0.2 g protein/kg BW in the next cycle, which again will be doubled within the third cycle to 0.4 g protein/kg BW. The control group will start with 0.05 g protein/kg BW. With the second cycle, patients receive 0.1 g protein/kg BW with further increase by 0.1 g protein/kg BW with every cycle until the amount of 0.4 g protein/kg BW is achieved. The protein target will be reached at the cumulative dose of at least 1.5 g protein/kg BW/24 h over 4 consecutive feeding cycles.

For calculation of our protein targets of participants with BMI > 18 to < 30, the actual body weight will be used. For participants with a BMI of 30–34.9 kg/m^2^, the target protein amount will be matched for an ideal weight with a BMI of 25 kg/m^2^. Hence, indicated flow rates in Tables 1 and 2 are calculated based on protein targets which are prioritised to energy targets during the acute phase of ICU stay.

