##### Day of inclusion (t_−1_)

We plan to perform the ultrasound and muscle biopsy on the day of study inclusion of eligible patients. Depending on time of ICU admittance, staff resources and opening hours of the Biobank storage, we will not always be able to do so. Therefore, if both the ultrasound and biopsy can be performed before 3:00 pm on the day of inclusion, enteral feeding will be initiated the next morning at 6:00 am. Otherwise, the procedures will be postponed to the next day and start of enteral feeding will be the following morning at 6:00 am. All standard laboratory parameters plus IGF-1 and interleukin-6 (for NUTRIC score) will be measured along with the morning routine laboratory of the next day. APACHE II, SAPS II and SOFA scores will be assessed within the first 24 h after ICU admission.

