#### Adverse event reporting and harms

Since the utilised enteral nutrition is the standard formula for the initial phase in ICU patients at the University Hospital Basel, no severe adverse events relating to the components of this formula are expected after careful enrolment following the specified exclusion criteria. All study patients will be monitored with respect to any possible adverse events related to the administration of enteral nutrition. An accountability log for the nutrition formula will be provided for each patient with the batch number of the administered bags.

Fresubin© Intensive comes under risk category A in our trial. It is a medicinal product authorised in Switzerland, and its use in this study is in accordance with the prescribing information: critically ill ICU patients with increased need for protein. Possible side effects of intermittent feeding in the intervention group are expected to be similar to the familiar side effects (e.g. meteorism, diarrhoea and constipation) of continuous feeding. The aspiration risk will be limited due to frequent controls of GRV after every feeding cycle. The enteral feeding will be stopped immediately in case any adverse events, including GRV > 300 ml, vomiting, regurgitation or aspiration, occur. Feeding will be restarted at the next planned cycle at the highest dose previously tolerated. If a patient of the experimental group does not tolerate the administered dose of nutrition over three consecutive feeding cycles (despite common prokinetics as 100 mg erythromycin and 10 mg metoclopramide, whenever no contraindication is applicable), he or she will be crossed-over to the standard continuous feeding group. If a patient of the CF group does not tolerate the administered dose of nutrition over three consecutive cycles, the treating physician will discuss how to proceed together with the study team.

For monitoring of hypo/hyperglycaemia, we will determine the blood glucose with an interval of 3 h maximum and if applicable administer insulin according to our standardised ICU protocol considering the state of health and presence of diabetes mellitus.

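### The glucose outcome is tied to a daily routine draw not aligned to feeding, so each arm is sampled at a different feeding phase, in an unknown direction

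*Protocol article*

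**What the plan says.** Three places in the protocol article deal with glucose measurement.

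- **Secondary outcome measures** lists glucose values in mmol/l with no sampling frequency. The next two items, urea and IGF-1, are each set at one value per day.
- **Glucose, urea and IGF-1 evolution over study period** is the only section that says how outcome glucose is collected: "Glucose, urea and IGF-1 will be measured together with daily routine blood analysis over the study period". No clock time is given. The word morning appears in the section on the day of inclusion, where the baseline set "will be measured along with the morning routine laboratory of the next day".
- **Adverse event reporting and harms** says, for monitoring of hypo- and hyperglycaemia, "we will determine the blood glucose with an interval of 3 h maximum" and "if applicable administer insulin according to our standardised ICU protocol". It does not say that these values form the outcome.

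The feeding schedules are fixed by the clock. The Table 1 footnote describes the intermittent cycles as "each with 30 min nutrition followed by a 4-h break and 30 min GRV measure, night time break of 4 h", and the Table 2 footnote describes the continuous cycles as "each with 5 h nutrition followed by a 30-min break and 30 min GRV measure, no night time break". Feeding starts at 06:00 in both arms.

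Under **Primary and secondary analysis**, the two-way repeated measures ANOVA chosen for protein is applied to all secondary outcomes. No term for time since feeding is stated.

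**The concern.** Glucose depends on when the patient was last fed, and in this trial that is what randomisation changes. A sample at a fixed hour therefore compares the arms at different points of their feeding cycles. Randomisation cannot balance this, because feeding phase at a given hour is determined by arm. Repeating the draw at the same hour each day repeats the same offset, so averaging over days does not remove it.

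The background section names better glucose control as an assumed advantage of intermittent feeding, and the objectives list blood glucose among the effects of intermittent feeding to be analysed. A once-daily sample could show an arm difference when glucose over the full 24 h is the same, or hide one that exists. Depending on the hour, it would miss the post-bolus peaks or catch little else.

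**Working it through.** **1. Reproduce the stated schedule totals.** The Table 1 footnote gives "Total time of feeding, 2 h; GRV measurements, 2 h; break, 20 h".

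- IF feeding: 4 × 0.5 h = 2 h. GRV: 4 × 0.5 h = 2 h. Break: 4 × 4 h + 4 h at night = 20 h. Sum: 24 h. This matches.
- CF feeding: 4 × 5 h = 20 h. GRV: 4 × 0.5 h = 2 h. Break: 4 × 0.5 h = 2 h. Sum: 24 h. This matches the Table 2 footnote.

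**2. Gaps between feeds.**

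- IF feeds run 06:00–06:30, 11:00–11:30, 16:00–16:30 and 21:00–21:30. Daytime gaps are 4.5 h. The overnight gap is 21:30 to 06:00 = 4 + 0.5 + 4 = 8.5 h.
- CF feeds run 06:00–11:00, 12:00–17:00, 18:00–23:00 and 00:00–05:00. Every gap is 1 h.

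**3. Time since feeding by assumed draw time.** The document gives no draw time, so a range is shown.

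| Draw | IF | CF |
|---|---|---|
| 04:00 | 6.5 h after feed | being fed |
| 05:00 | 7.5 h | 0 h (feed just ended) |
| 05:30 | 8.0 h | 0.5 h |
| just before 06:00 | 8.5 h | 1 h |
| 06:15 | bolus running | being fed |
| 07:00 | 0.5 h after bolus | being fed |
| 08:00 | 1.5 h after bolus | being fed |
| 10:00 | 3.5 h after bolus | being fed |

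At 06:15 both arms are being fed, but not at the same rate. At the Day 2 dose, IF gets 0.4 g/kg ÷ 0.5 h = 0.8 g/kg/h of protein and CF gets 0.4 ÷ 5 h = 0.08 g/kg/h, a tenfold difference. None of these draw times puts the arms in the same phase, and the contrast changes character at 06:00.

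**4. What the 3-hourly values would give.** 24 h ÷ 3 h = at least 8 values per day, or 8 × 7 = 56 over seven full days, against 7 routine values. On a grid of 00:00, 03:00, …, 21:00, the IF values fall 2.5, 5.5, 0, 2.5, 0.5, 3.5, 1.5 and 0 h after feeding (0 = feed running). The CF values are all taken during a feed or at the moment one ends or starts. The IF series now covers the cycle instead of one point of it.

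**5. Illustration of consequence (all inputs assumed).** Take SD 2 mmol/l, within-patient correlation 0.5, 7 daily values, 30 per arm and a two-sided t test on patient means.

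- Variance factor: (1 + 6 × 0.5) ÷ 7 = 0.571.
- Standard error of the difference: √(2 × 4 × 0.571 ÷ 30) = 0.39 mmol/l.
- A pre-06:00 draw on day 1 precedes any study feeding, so at most 6 of 7 values carry the offset and the mean shift is 6/7 of it.

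Chance that a pure phase offset is declared significant:

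| Assumption | 0.5 mmol/l | 1.0 mmol/l | 1.5 mmol/l |
|---|---|---|---|
| SD 2, alpha 5%, 6 of 7 days | 19% | 58% | 90% |
| SD 2, alpha 5%, all 7 days | 24% | 71% | 96–97% |
| SD 3, alpha 5%, 6 of 7 days | 11% | 30% | 58% |
| SD 2, alpha 1%, 6 of 7 days | 7% | 33% | 73% |

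These figures show only that a modest offset could matter at this sample size. They do not estimate what will happen. They also ignore insulin, which could shrink the offset.

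**The case against.** The strongest reply is that the protocol does not confine the outcome to one sample. It sets urea and IGF-1 at one value per day but leaves glucose without a frequency, it has glucose determined at least every 3 h, and it leaves detailed methods to a statistical analysis plan that is not shown. Choosing a summary measure is ordinary work for that plan. Insulin under a standard ICU protocol may also dampen differences between feeding phases, and glucose is not part of the stated hypothesis.

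Much of this stands. It is why the point is about a measurement left badly fixed, and not a demonstrated bias. It does not dispose of the matter. The section on how the outcome is collected makes a positive choice, the routine draw, and groups glucose with two once-daily analytes. The 3-hourly values appear only under safety monitoring. An analysis plan that used them would have to depart from the stated collection method.

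A reader might infer more: that the sample always falls in a long fast for intermittent patients and just after feeding for continuous patients, so intermittent feeding is flattered. The document does not support that. The pattern needs a draw before 06:00. No draw time is given, and morning is mentioned only for the baseline set. From 06:00 the intermittent patient is in or just after a bolus, and the bias could run the other way. Nor does any figure in the document show that the contrast would reflect draw time alone and nothing of glucose control.

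**Conclusion.** The concern holds in this form: as written, the glucose outcome rests on a daily draw whose feeding phase differs systematically by arm, and the stated analysis has nothing to remove that difference. The separation is up to 8.5 h against at most 1 h since feeding for a draw before 06:00. After 06:00 it is a bolus in progress or recently finished against continuous delivery. The direction is unknown because the draw time is unknown. The size in mmol/l cannot be derived from the document, and the percentages above are illustrations on assumed inputs.

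Separately, one value a day cannot describe glucose over a cycle of four boluses, and the three sections leave open which values are compared.

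This concerns one secondary outcome. The primary outcome and N = 60 are untouched. It is worth correcting because the remedy needs no extra sampling.

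**What to change.** In the list of secondary outcome measures and in the section on glucose, urea and IGF-1, define the glucose outcome from the values already determined at least every 3 h in both arms. A suitable definition is a 24-h time-weighted mean per study day, with the daily maximum or a measure of within-day variability, and with daily insulin dose reported alongside. Keep the routine-draw glucose as descriptive only, with its clock time recorded. Urea and IGF-1 can stay at one value per day.

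The cost is export of bedside glucose and insulin values to the eCRF and slightly more data handling. The protocol says that glucose is determined at these intervals but not that every value reaches the eCRF, so the sponsor should confirm that the values can be retrieved with time stamps. No blood sampling, feeding schedule or patient care changes.

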##### Assessment of study scores

The study team will assess and calculate standardised scores such as APACHE II, SAPS II and NUTRIC once within 24 h after ICU admission. The SOFA score will be assessed daily until closeout.

#### Plans to promote participant retention and complete follow-up

The defined eligibility criteria lead to participant retention due to inclusion of patients expected to stay at least 5 days in ICU.

In case of study withdrawal or early discharge within days 1–4 of the study, all data will be destroyed, and the patient will be replaced. Except for patients with early discharge to the general ward (e.g. before study day 5), the study team will attempt to continue the study: all study procedures will be continued including allocated feeding protocol, study laboratory and the ultrasound and muscle biopsy on day 7 of the study. If there is no possibility to continue enteral feeding on general ward, the patient will be replaced.

If the patient is discharged on day 5 or 6 of the study, we will perform the ultrasound and muscle biopsy on the day of discharge and accept missing data of the residual day(s).

If the patient is withdrawn from the study within days 5–7 of the study, the patient or his next of kin will be asked for use of the data already recorded. If applicable, we will also ask for use of regular data registered thereafter in the ICU setting.

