### Additional consent provisions for collection and use of participant data and biological specimens

As stated previously, in the consent form, participants will be asked if they agree to use of their data should they choose to withdraw from the trial. Participants will also be asked for permission for the research team to share relevant data with people from the Universities taking part in the research or from regulatory authorities, where relevant. This trial involves collecting biological specimens for storage.

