#### Criteria for discontinuing or modifying allocated interventions

Participants will be withdrawn from the study in case of the following:
Death or rapid recovery/dischargeOn demand of the patient or his/her next of kinOn demand of the treating physician or the study team (e.g. safety reasons, please see the “Adverse event reporting and harms” section)

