#### Data management

Study data will be collected and managed using REDCap electronic data capture tools hosted at University Hospital Basel [50]. REDCap is a secure, web-based application designed to support data capture for research studies. REDCap provides (1) an intuitive interface for validated data entry, (2) audit trails for tracking data manipulation and export procedures, (3) automated export procedures for seamless data downloads to common statistical packages and (4) procedures for importing data from external sources.

All data, including demographic data, visit dates, randomisation number and serious adverse events (SAEs), related to this study will be kept within the trial master file (TMF) and the REDCap eCRF. A unique patient study code will be assigned to every screened patient consisting of the prefix PBN (Pro BoNo) plus consecutive numbering for every included patient (e.g. PBN-1). This code will be used to identify all study-specific data (e.g. ultrasound images, blood parameters). The trial will be terminated after collecting data from 30 patients in each group. The signed informed consent forms will be kept in the investigator site file (ISF). To minimise bias, we will set range checks for data values within the eCRF. Data will be archived dually on an external hard disk and on our in-house server system with a backup every 24 h. The hard disk and all physical study data will be stored in a designated place on our ICU at the University Hospital Basel for a minimum of 10 years after study termination or in case of premature termination of this study.

SAEs will be documented in the REDCap eCRF and on paper documents.

Only the study team will have access to study-related data. In case of a patient’s ex post denial of study participation, the data collected will not be used for publication in the present trial or in future trials. In such cases, the data will be destroyed.

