##### Datasets to be analysed, analysis populations

An intention-to-treat and per protocol analysis of ICU patients who meet all inclusion and no exclusion criteria will be performed.

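### Destroying the data of patients withdrawn or discharged early on days 1–4, and replacing them, selects the analysed set after randomisation and rules out the promised intention-to-treat analysis

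*Protocol article*

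**What the plan says.** The rule stands in the protocol article under Plans to promote participant retention and complete follow-up. On study withdrawal or early discharge "within days 1–4 of the study, all data will be destroyed, and the patient will be replaced". An exception follows: "Except for patients with early discharge to the general ward (e.g. before study day 5), the study team will attempt to continue the study". The wording is awkward, but the rest of the sentence, which lists continued feeding, laboratory tests, ultrasound and biopsy, shows that ward patients are meant to stay in the study. The exception ends where ward feeding is impossible: "If there is no possibility to continue enteral feeding on general ward, the patient will be replaced".

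Who counts as withdrawn is set under Criteria for discontinuing or modifying allocated interventions: "Participants will be withdrawn from the study in case of the following". The list covers death, rapid recovery or discharge, the wish of the patient or next of kin, and the request of the treating physician or study team, for example for safety. The blinding section says that neither of those teams can be blinded.

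The analysis populations are defined thus: "An intention-to-treat and per protocol analysis of ICU patients who meet all inclusion and no exclusion criteria will be performed". Recruitment ends on retained patients: "The trial will be terminated after collecting data from 30 patients in each group". The missing-data section relies partly on replacement to keep missing data low, and rules out imputation.

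On withdrawal, the consent section states that "participants will be asked if they agree to use of their data should they choose to withdraw from the trial".

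**The concern.** Intention-to-treat means that everyone randomised is analysed in the arm assigned. Here a group of randomised patients is removed because of what happened to them after allocation, and their records are erased. The usual repair, an analysis plan that defines the population properly, is not available, because destroyed data cannot be analysed.

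The reasons for removal are not neutral. Death, rapid recovery and safety withdrawal may be related to feeding mode or to how much protein a patient could take, and some removals are decided by staff who know the allocation. If exits differ between arms, in frequency or in the kind of patient who leaves, the comparison of the 30 and 30 who remain is no longer protected by randomisation.

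**Working it through.** **1. Does the rule delete observed primary outcomes?** The outcome is hours from the first study feed until at least 1.5 g protein/kg over 24 h, over four consecutive cycles. Formula: 24-h total = sum of the last four doses in Tables 1 and 2, with feeding starting at 06:00 on day 1.

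- Intermittent arm. Day 1 doses are 0.1, 0.2, 0.4, 0.4; day 2 doses are 0.4 each. After day 2 cycle 1: 0.2 + 0.4 + 0.4 + 0.4 = 1.4. After cycle 2: 4 × 0.4 = 1.6, so the target is met. The feed ends at 29.5 h, or 34 h once the break and residual check are complete.
- Continuous arm. Day 1 doses are 0.05, 0.1, 0.2, 0.3; day 2 doses are 0.4 each. After day 2 cycle 1: 0.1 + 0.2 + 0.3 + 0.4 = 1.0. After cycle 2: 0.2 + 0.3 + 0.4 + 0.4 = 1.3. After cycle 3: 0.3 + 3 × 0.4 = 1.5, so the target is met. The feed ends at 41 h, or 42 h with the break and residual check.

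These sums match the running totals printed in both tables. Both times fall on day 2 (24–48 h). A patient fed to schedule who leaves on day 3 or 4 therefore has an observed primary outcome, and the rule erases it. A patient who leaves before target loses partial follow-up.

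**2. How many patients could disappear?** The protocol gives no early-exit rate, so d is an assumption. If patients are replaced until 60 are kept, the number randomised is 60/(1 − d), rounded up.

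| Assumed exit, days 1–4 | Randomised | Data destroyed |
|---|---|---|
| 5% | 64 | 4 |
| 10% | 67 | 7 |
| 15% | 71 | 11 |
| 20% | 75 | 15 |
| 30% | 86 | 26 |

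**3. When does this bias the comparison?** Illustrative simulation with no true effect: standard normal outcome, 30 retained per arm, patients with low values on a variable correlated with the outcome leave and are replaced, two-sample t test at the protocol's 0.01 level, 4,000 runs. Exit rates and correlations are assumptions, and the test is simpler than the planned ANOVA.

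| Exit, arm A / arm B | Exit–outcome correlation, A / B | Bias (SD) | Rejection, retained only | Rejection, all randomised |
|---|---|---|---|---|
| 20% / 20% | 0.5 / 0.5 | 0.00 | 0.010 | 0.012 |
| 20% / 10% | 0.5 / 0.5 | 0.07 | 0.014 | 0.012 |
| 30% / 10% | 0.5 / 0.5 | 0.15 | 0.022 | 0.011 |
| 30% / 10% | 0.7 / 0.7 | 0.21 | 0.044 | 0.010 |
| 30% / 10% | 0.7 / 0 | 0.35 | 0.12 | 0.009 |

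Equal exit with equal dependence does no harm to the error rate. Bias appears when the arms differ in exit rate or in the link between exit and outcome. Its sign depends on who leaves: here poor performers leave; if patients who recover fast leave instead, it reverses.

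**4. Do other sections agree with the rule?**

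- The consent provisions ask participants whether their data may be used after withdrawal; the retention rule leaves nothing to ask about on days 1–4. For withdrawals on days 5–7 the retention section itself asks permission.
- Data management says that study data, including serious adverse events, are kept and archived for at least 10 years. The one ground for destruction it names is later denial of participation.
- The serious adverse events section requires deaths and pulmonary aspirations to be documented and reported.

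None of these fits the destruction of all data.

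**The case against.** Several stronger readings are tempting, and the document does not support them.

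- *Intolerance or aspiration leads to deletion.* The adverse event section handles intolerance by restarting at the next cycle and, after three failed cycles, by crossover (intermittent arm) or discussion (continuous arm). None of this is called withdrawal. Aspiration patients are followed to hospital discharge. What remains is discretionary safety withdrawal.
- *Early harms vanish.* The sections on data management and serious adverse events require deaths and aspirations to be kept and reported. The text contradicts itself; it does not settle that the destruction rule prevails.
- *Everyone discharged early is erased.* Ward patients with continued feeding are kept, and for those who cannot be fed there the text repeats replacement but not destruction.
- *Death is expressly covered.* The retention section does not name it. Death comes in through the list of withdrawal reasons.
- *The primary outcome is always known by day 2.* Intake is volume given minus half the residual volume. In the continuous arm the total after day 2 cycle 3 is exactly 1.5, so any recorded residual postpones the target. In the intermittent arm the margin is 0.1 g/kg: for an assumed 70 kg patient that is 7 g, or 70 ml of formula at 10 g per 100 ml, so more than 140 ml of residual over four cycles postpones it. Some who leave on day 3 or 4 will have no observed outcome.

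The rule also has an understandable motive. The sample size rests on 20 time points (four a day for 5 days), and a repeated measures ANOVA works most simply on complete series. That explains a wish for patients with 5 days of data. It does not justify destroying the records of the others or calling the result intention-to-treat.

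**Conclusion.** The point holds in this scope: the rule as written, joined to the withdrawal list and the stop at 30 patients with data per group, makes the stated intention-to-treat analysis impossible and erases primary outcomes for patients fed to schedule who leave on day 3 or 4. This follows from the text and the feeding tables without any assumed rate. It must be corrected in the protocol, since no later analysis plan can restore the data.

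The size and direction of bias are unknown. The 7–15 lost patients rest on an assumed 10–20% exit, and the rejection rates of 0.01 to 0.12 rest on assumed differences between arms. A reader might infer that the rule favours intermittent feeding; nothing in the protocol shows that. Whether early serious adverse events stay in the trial dataset is unreconciled, not decided.

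**What to change.** - Delete the automatic destruction rule for days 1–4. Destroy data only where the patient or next of kin refuses its use.
- Define the intention-to-treat set as every randomised patient, with data up to exit. Base the end of recruitment on patients randomised, not on patients retained.
- For time to target, count death or the end of enteral feeding before target as target not reached, or pre-specify censoring with a sensitivity analysis.
- Keep all serious adverse events in the safety set, whatever the day of exit.
- If more patients are needed for the day-7 muscle outcomes, add them to those already randomised; do not substitute them.
- Recruitment began in March 2019, so report how many patients have already been replaced, by arm and, where known, by reason.
- Reconcile the sections on consent provisions, retention, data management, analysis populations, missing data and serious adverse events.

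Cost: a protocol amendment, some incomplete day-7 data, and a primary analysis that handles incomplete follow-up. The last is more than a wording change, because the planned repeated measures ANOVA without imputation does not readily accommodate patients who leave early. No new study procedures are needed. Data already destroyed cannot be recovered.

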## Methods: participants, interventions and outcomes

### Study setting

Patients will be observed for a maximum of 7 days during their stay in an adult 50-bed ICU admitting medical or surgical patients.

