#### Participant timeline

The study period consists of screening and enrolment, allocation, observation time and closeout. Screening and enrolment will be performed within 48 h after ICU admission. Allocation is defined as the day of start of enteral feeding. Closeout is defined as the end of the seventh day of observation (or day of discharge from the ICU, if earlier than 7 days).

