##### Serious adverse events

Many ICU patients suffer from various adverse events that are life-threatening and/or prolong existing hospitalisation. Therefore, we will only document and report pulmonary aspiration (defined as evidence of nutrition formula within the tracheo-bronchial branches) or death of patients as SAE.

The occurrence of abovementioned SAEs will be assessed during every ICU shift. The sponsor must report all changes in research activity and unanticipated problems to the responsible ethics committee. Likewise, all SAEs must be reported within 7 days if fatal, otherwise within 15 days. The sponsor will provide an annual safety report.

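### For patients moved to the ward before day 5, study feeding may run to day 7 while closeout falls on ICU discharge and no ward route for SAE assessment is stated

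*Protocol article*

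**What the plan says.** All places are in the Protocol article.

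- **Plans to promote participant retention and complete follow-up.** Withdrawal or early discharge in days 1 to 4 normally leads to replacement. Patients who go to the general ward before day 5 are the exception. For them the team will try to carry on, and "all study procedures will be continued including allocated feeding protocol, study laboratory and the ultrasound and muscle biopsy on day 7 of the study". If enteral feeding cannot continue on the ward, the patient is replaced.
- **Participant timeline.** Closeout is the end of the seventh observation day, "or day of discharge from the ICU, if earlier than 7 days".
- **Study setting.** "Patients will be observed for a maximum of 7 days during their stay in an adult 50-bed ICU".
- **Criteria for discontinuing or modifying allocated interventions.** Discharge is among the reasons for withdrawal from the study.
- **Serious adverse events.** Of SAEs, "we will only document and report pulmonary aspiration" and death. The method of finding them is: "The occurrence of abovementioned SAEs will be assessed during every ICU shift".
- **Study period** and **Table 3.** The study period is 7 days from the start of enteral feeding. SAEs are marked on each of days 1 to 7, and the day 7 column is headed as closeout.

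**The concern.** A patient moved to the ward on day 3 is closed out on day 3 under Participant timeline, yet stays on the randomised feeding regimen until day 7 under the retention section. Both cannot be followed. The one SAE procedure that the article describes is a check at each ICU shift, which cannot be carried out on a ward, and no ward equivalent is named.

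This matters because aspiration and death are the only SAEs that the trial records, and the Discussion (Intervention) treats aspiration as the gravest adverse event of enteral feeding. Patients continued on the ward are not replaced, so they stay in the comparison of the two regimens. If staff apply the closeout definition literally, an aspiration or death during continued study feeding may not be looked for, or may be found and then classed as after the end of participation. The 7-day and 15-day reports to the ethics committee depend on the event being recognised as a study SAE.

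**Working it through.** The plan gives no figure on this point, so the check sets the sections side by side and then counts the feeding exposure concerned.

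**1. Which rule applies to a patient moved to the ward at the end of day 3?**

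| Section | Consequence for this patient |
|---|---|
| Retention and follow-up | Allocated feeding, laboratory tests, and day 7 ultrasound and biopsy continue |
| Participant timeline | Closeout on day 3 |
| Discontinuation criteria | Discharge is a reason for withdrawal |
| Study setting | Observation takes place during the ICU stay |
| Day 7 of observation | Closeout visit on day 7 |
| Study period | Runs 7 days from first feed |
| Table 3 | SAEs on days 1 to 7, last column labelled closeout |
| Serious adverse events | Check at each ICU shift; no ward check given |

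The retention section, the Study period section, the Day 7 section and the day numbering of Table 3 point to day 7. Participant timeline, the discontinuation criteria and Study setting point to ICU discharge. Table 3 does not settle the matter, because its last column is labelled with the very term that Participant timeline moves to ICU discharge.

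**2. Is there another route for each SAE?**

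- *Aspiration:* yes. It is a secondary outcome counted per feeding cycle, and the bedside protocol described under Strategies to improve adherence to interventions has space for adverse events in every cycle, with daily checks by the study team. The article does not say that this form moves to the ward with the patient.
- *Death:* no separate route. On the ward it rests on Table 3 and on the general statement that all study procedures continue.

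**3. Feeding exposure in the disputed window.** Tables 1 and 2 give 4 cycles per 24 h in both arms.

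- Total over the study period: 4 × 7 = 28 cycles.
- Cycles left after transfer at the end of day d: 4 × (7 − d).

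| Transfer at end of day | Cycles left | Share of 28 |
|---|---|---|
| 1 | 4 × 6 = 24 | 86% |
| 2 | 4 × 5 = 20 | 71% |
| 3 | 4 × 4 = 16 | 57% |
| 4 | 4 × 3 = 12 | 43% |

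**4. Weight of one event.** With 30 patients per arm, 1/30 = 3.3 percentage points. This shows scale only; it does not estimate events missed.

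**5. Discharge on day 5 or 6.** The final ultrasound and biopsy are done on the day of discharge, and the text does not say that study feeding goes on. No gap is shown for these patients.

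**The case against.** The strongest reply is that the protocol plainly means to collect safety data on the ward. The retention section says that all study procedures continue and names feeding, laboratory tests and biopsy only as examples; SAE recording is a scheduled procedure in Table 3. The study period is 7 days with no ICU limit, so the follow-up of aspiration to hospital discharge (Provisions for post-trial care) can be read to cover an aspiration on the ward. The early-closeout clause fits the day 5 or 6 discharge rule, and the specific ward rule may be taken to override it. The group may also be very small: inclusion requires an expected ICU stay and expected enteral feeding of at least 5 days, and continuation is only attempted. Finally, this is a condensed article, and ward staffing is the sort of detail that a full protocol would hold.

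Most of this stands, and it limits the point. A reader might infer that SAEs are sought solely at ICU shifts, that ward events go uncollected, or that the aspiration rate is understated. The documents do not support this. The word "only" in the SAE section restricts which events count, not where they are sought, aspiration has a per-cycle route, and no rate of early transfer is given.

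A reader might also infer that gastric residual volume and glucose checks stop at the ICU door. The text does not say so. Residual volume is checked after every cycle, and where the plan states "we will determine the blood glucose with an interval of 3 h maximum", the reference to an ICU protocol qualifies insulin administration, not the glucose interval.

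What the reply does not remove is the contradiction. The closeout definition has no exception for ward-continued patients, discharge is listed as withdrawal, and the stated SAE check cannot be done where these patients are. These are statements in the article that conflict, not details left out of it.

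**Conclusion.** The point holds as a contradiction between stated rules, with a possible loss of safety data. For patients discharged to the ward before day 5, collection to day 7 appears intended, but the closeout definition contradicts it and no ward route for SAE assessment is stated, least of all for death. Events during continued study feeding may be missed or treated as outside the window.

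For a patient transferred at the end of day 3 or 4, the disputed window holds 16 or 12 of 28 scheduled cycles (57% or 43%), and more if transfer is earlier. This assumes that feeding does continue on the ward to day 7 on the 4-cycle schedule. The number of patients concerned cannot be derived, so neither the number of events at risk nor any bias between arms can be estimated. The correction is worth making because, read literally, the rules would end safety collection while randomised feeding goes on, and repairing them costs almost nothing.

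**What to change.** Reconcile Study setting, Criteria for discontinuing or modifying allocated interventions, Participant timeline, Plans to promote participant retention and complete follow-up, Serious adverse events, and Table 3, as follows:

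1. Define closeout for a patient who continues on the ward as the end of day 7, or the last study feed or study procedure if that comes earlier, and not as ICU discharge. Label the last column of Table 3 to match.
2. Make clear that discharge to the ward with study feeding continued is not a withdrawal for purposes of data collection. Whether and how feeding continues on the ward is for the sponsor to settle; the collection window should follow whatever is decided.
3. Word the SAE rule as assessment every shift, on ICU or ward, for as long as study feeding continues, covering both aspiration and death.
4. State that the per-cycle bedside form goes with the patient.

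The cost is protocol wording and a little extra documentation by ward staff, probably for few patients. The study team already has to follow these patients for laboratory values and the day 7 ultrasound and biopsy.
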